#### Moderation analyses

Moderation analyses will explore the differential effectiveness of the two interventions by maternal level of education (as a proxy for SES), child race/ethnicity, and technician ESDM fidelity. We will build upon the primary models with treatment group by time effects by incorporating interaction terms for moderators of interest and conducting sub-group analyses. For each target moderator (e.g., maternal education), we will add the 3-way treatment group by time by moderator interaction term (and all lower-order 2-way and main effects) to determine whether differences between treatment groups in change over time for a given outcome variable are modified by target moderators. A significant 3-way interaction effect will indicate the presence of treatment effect heterogeneity between subgroups. Following this, we will conduct simple effect analysis to estimate treatment effect differences (i.e., difference in changes over time between arms) within each subgroup. For adherence to ESDM fidelity at the technician level, we expect substantial differences between treatment groups, and plan to investigate this as a moderator of all child outcomes.

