**Fig. 1 Fig1:**
[figure not shown]
Applying the Exploration, Preparation, Implementation, Sustainment (EPIS) Conceptual Model of Implementation to ASD EBI

The current project uses a hybrid type 1 randomized controlled design to examine ESDM effectiveness and to gather data on implementation determinants. This study will test the effectiveness of ESDM for improving social communication and language (primary), adaptive behavior, goal progress and quality of life (secondary) outcomes in a diverse community sample of autistic children. Our research question include: (1) Compared to usual EBI, do children in the ESDM condition demonstrate significantly increased growth rates in social communication and language? (2) Do caregivers in the ESDM condition have greater increases in use of general NDBI strategies and greater caregiver competence than those in EBI? (3) Does ESDM engage the treatment mechanisms of child social motivation and caregiver fidelity within both treatment groups? (4) Do variable such as caregiver education, child race/ethnicity and provider adherence to ESDM fidelity moderate child progress in both groups? We will use the EPIS framework to gather data on ESDM Implementation outcomes including acceptability, feasibility, appropriateness (including for children), cultural responsivity, CBA provider ESDM fidelity, and caregiver engagement.

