#### Technician participants

Technicians supervised by a participating supervisor and working with an enrolled child/family will be recruited. Inclusion criteria include planning to be employed at the agency for at least 12 months and have not had previous ESDM training.

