#### Use of NDBI strategies

To understand treatment differentiation between the ESDM and EBI groups we will code the use of NDBI strategies across groups. To examine differentiation between the interventions in a more valid and unbiased manner than simply using ESDM codes across conditions we will use the eight-item NDBI-Fi measure [90] developed to capture common elements across NDBI interventions. This measure has adequate reliability, sensitivity to change, and concurrent, convergent, and discriminative validity. We will use the total score and examine differences by strategy type, responsiveness, and directives, consistent with recent studies [91].

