#### Mediation analyses

Conceptually, social motivation (measured by PDDBI and JERI) and caregiver NDBI fidelity can be viewed as an intermediated outcome (mediator, M). The intervention may affect the primary outcomes indirectly through a pathway of the mediator (M). To test the mediated effect (or mechanism of change), we will conduct a mediation analysis by extending the generalized mixed effects models specified for assessing treatment group differences in primary outcome variables by adding continuous ratings of social motivation and parent fidelity, respectively, as predictors to the model describing language improvement. The mediation analysis will follow a standard series of steps: (1) Test for the direct effect of the treatment group on the primary outcome variable as represented by the time by treatment group interaction effects (i.e., the primary model); (2) Test for the time by treatment group interaction effect using the measure of social motivation (or parent fidelity, respectively) as the dependent variable in an analogous mixed effects model to assess the coefficient for group differences in change over time in the target mediator; (3) Return to the model in step 1 and add the main effect of time-varying social motivation scores (or parent fidelity, respectively) in predicting outcome scores to assess the direct relationship between the target mediator and outcome while controlling for the time by treatment group effect on outcome; (4) Calculate the degree and significance of the indirect effect using Monte Carlo simulations of the estimated coefficients and their respective standard errors.

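### Technician ESDM fidelity is produced by the randomised training, yet it is analysed as a moderator, so the stated reading of its three-way term as treatment effect heterogeneity is wrong

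*Protocol article*

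**What the plan says.** Under Moderation analyses, the protocol article names three moderators: maternal education, child race/ethnicity and technician ESDM fidelity. One model serves every target moderator: "we will add the 3-way treatment group by time by moderator interaction term". One reading is fixed in advance: "A significant 3-way interaction effect will indicate the presence of treatment effect heterogeneity between subgroups". Arm differences in change are then to be estimated within each subgroup. On fidelity the section adds: "For adherence to ESDM fidelity at the technician level, we expect substantial differences between treatment groups, and plan to investigate this as a moderator". The section's status is exploratory: "Moderation analyses will explore the differential effectiveness of the two interventions". Research question 4, at the end of the Background, likewise asks whether caregiver education, race/ethnicity and "provider adherence to ESDM fidelity moderate child progress in both groups".

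Other sections show where technician fidelity comes from. Technicians qualify only if they "have not had previous ESDM training" (Technician participants). Those in ESDM regions then receive the didactic course, supervisor coaching and micro-lessons (Technician training). EBI regions carry on with their existing practice (Usual early behavioral intervention).

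Under Mediation analyses, step 3 is to "add the main effect of time-varying social motivation scores (or parent fidelity, respectively) in predicting outcome scores", and step 4 tests the indirect effect by Monte Carlo simulation. No lag is named. Table 2 schedules the mediators and the primary outcomes at the same three visits.

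**The concern.** An effect moderator splits the trial into subgroups that exist whatever the assignment. Maternal education and race/ethnicity do that. Technician ESDM fidelity does not: it arises after randomisation and because of it, and the protocol itself expects the arms to differ substantially.

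Comparing arms at the same fidelity level therefore sets ESDM technicians who took up little of the training against EBI technicians who happen to score high without it. Those technicians and their caseloads may differ in skill, setting or child characteristics, and randomisation no longer balances them. Under the stated rule, a significant term would still be reported as a treatment that works differently in different subgroups. Readers planning scale-up could take it as showing how much fidelity is needed for benefit.

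The mediation question is related but smaller. Randomisation protects the path from treatment to mediator. It does not protect the path from mediator to outcome, and step 3 as ordinarily read takes both from the same visit.

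**Working it through.** **1. The protocol's own figure.** The only power statement concerns the primary effect: at least 80% at d = 0.6. None is given for moderation or mediation. The check reads the 20 centers as 20 randomised regions (10 per arm), with 50 teams and 135 children per arm (270 of 300 after 10% dropout). At the least favourable stated ICCs (region 0.1, team 0.25):
- Variance per arm = 0.1/10 + 0.25/50 + 0.65/135 = 0.0198.
- SE of the difference = √(2 × 0.0198) = 0.199.
- Power = Φ(0.6/0.199 − 1.96) = 0.854, or 0.813 with a t reference on 18 df.

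The statement reproduces, and nothing below changes it.

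**2. Is fidelity a baseline variable?** No prior ESDM training at entry, training after assignment in one arm only, and an expected substantial arm difference together make it a consequence of assignment. A baseline fidelity score, being unaffected by training, would not be expected to differ substantially by arm.

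**3. Common support (assumed separations).** For two normal distributions with equal SD whose means lie d SD apart, overlap = 2Φ(−d/2):
- d = 1: 62%
- d = 2: 32%
- d = 3: 13%
- d = 4: 5%

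This bears on the arm contrasts within fidelity levels. The three-way term itself is a difference of within-arm slopes and does not need overlap.

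**4. Can the slope mislead on its own? An illustration with assumed inputs.** The true treatment effect is 0.6 for everyone. Technician skill S (SD 1) adds 0.2S to child change in both arms, so nothing modifies the effect. Skill raises fidelity only among the trained: ESDM fidelity = 4.0 + 0.4S + noise (SD 0.2); EBI fidelity = 2.0 + noise (SD 0.3).
- ESDM slope of change on fidelity = 0.2 × 0.4/(0.4² + 0.2²) = 0.2 × 2 = 0.40. EBI slope = 0. Expected spurious interaction = 0.40.
- Apparent effect at mid-range fidelity of 3 = 0.6 + 0.40 × (3 − 4) = 0.20, against a true 0.6.
- Simulation (100 teams, 3 children each, 500 runs): mean interaction 0.40, rejected in 17% of runs at nominal 5%; mean effect at fidelity 3 was 0.18; 0.4% of teams lay in the overlap region.

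That separation is extreme. The pooled SD is √((0.20 + 0.09)/2) = 0.381, so the arms lie 2/0.381 ≈ 5.3 SD apart. With the same slopes but separations of 2 or 3 SD, the midpoint lies 0.381 or 0.571 below the ESDM mean. The apparent effect there is 0.6 − 0.40 × 0.381 = 0.45, or 0.6 − 0.40 × 0.571 = 0.37. The spurious slope of 0.40 does not depend on separation.

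**5. Mediation steps, simulated.** Assumed: 300 children, three visits, child random intercept, no team or region clustering, 100 runs per scenario, same-visit mediator.

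| Scenario | Mean indirect / total | Significant |
|---|---|---|
| No mediator effect, same-visit common cause | 0.166 / 0.402 | 96% |
| No mediator effect, language drives motivation | 0.118 / 0.413 | 53% |
| Genuine mediator | 0.159 / 0.394 | 95% |

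The first and third rows are practically indistinguishable from the output.

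**The case against.** **On moderation.** The analysis is worded as exploratory, two of the three moderators are sound, and the primary test is untouched. All of that stands and limits the weight of the point. It is also true that the interaction slope needs no overlap, that the article gives no fidelity distribution, and that the illustration was built to show the bias. The objection survives because the interpretive rule is written into the article and cannot be right for a variable that training produces.

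A reader might infer that the protocol disowns ESDM codes for any between-arm use, since it prefers another tool "in a more valid and unbiased manner than simply using ESDM codes across conditions". That sentence concerns treatment differentiation only and does not settle the moderation question.

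**On mediation.** The words same visit do not appear; the reading rests on unlagged time-varying scores and a shared schedule. An article may leave a lag to the analysis plan. Shared measurement error is also limited. JERI or NDBI-Fi with Vineland, and PDDBI with APPL, share neither informant nor method. Coders are each trained in one system and are naïve to group and timepoint. These points stand, which is why this part is secondary.

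A reader might also infer that most trials with no mediator effect would declare mediation. The documents give no inputs for such a rate. Once a same-visit correlation is assumed, the rate mostly returns the power of the treatment-to-mediator path: an assumed effect of 0.6 with SE 0.2 gives Φ(3 − 1.96) = 0.85 by itself.

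Nor do research questions 3 and 4 fail as a whole. Question 3, on engaging the mechanisms, is answered by the randomised comparison in step 2. Only the fidelity part of question 4 is affected.

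**Conclusion.** The point holds for technician ESDM fidelity. It is a post-randomisation variable placed in a model, and under an interpretive rule, suited to baseline moderators. Arm contrasts within fidelity levels are not randomised comparisons. They would rest on 32% or 13% overlap if the arms were 2 or 3 SD apart, which is an assumed range. The conclusion itself does not depend on that range; it follows from how fidelity arises.

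For mediation, the narrower conclusion is that a significant indirect effect from the unlagged model shows association and cannot by itself distinguish mediation from reverse causation or common causes. This rests on the ordinary reading of step 3. The claim that no mechanism analysis is informative would go beyond the documents.

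Maternal education, race/ethnicity, the step 2 tests and the primary intent-to-treat comparison with its power are unaffected.

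**What to change.** 1. Remove technician ESDM fidelity from the three-way moderation models and the simple-effect analyses, keep only baseline variables as moderators, and reword research question 4 to match.
2. Analyse technician fidelity as an outcome or mediator, or as a dose-response within the ESDM arm labelled observational. The exploratory implementation analysis already plans to model provider fidelity as a dependent variable.
3. Label the indirect effect from the time-varying model as associational. Add a supporting analysis in which the 6-month mediator, adjusted for its own baseline and the baseline outcome, predicts the 12-month outcome, with a sensitivity analysis for mediator-outcome confounding.

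The cost is analysis wording; the visits and measures are already scheduled. The lagged analysis uses one interval and so has less power. It strengthens temporal order but does not guarantee causal identification. Further adjustment for the 6-month outcome would be a trade-off, because it conditions on another post-randomisation variable and removes any mediated effect already realised by then.

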#### Mediation analyses

Conceptually, social motivation (measured by PDDBI and JERI) and caregiver NDBI fidelity can be viewed as an intermediated outcome (mediator, M). The intervention may affect the primary outcomes indirectly through a pathway of the mediator (M). To test the mediated effect (or mechanism of change), we will conduct a mediation analysis by extending the generalized mixed effects models specified for assessing treatment group differences in primary outcome variables by adding continuous ratings of social motivation and parent fidelity, respectively, as predictors to the model describing language improvement. The mediation analysis will follow a standard series of steps: (1) Test for the direct effect of the treatment group on the primary outcome variable as represented by the time by treatment group interaction effects (i.e., the primary model); (2) Test for the time by treatment group interaction effect using the measure of social motivation (or parent fidelity, respectively) as the dependent variable in an analogous mixed effects model to assess the coefficient for group differences in change over time in the target mediator; (3) Return to the model in step 1 and add the main effect of time-varying social motivation scores (or parent fidelity, respectively) in predicting outcome scores to assess the direct relationship between the target mediator and outcome while controlling for the time by treatment group effect on outcome; (4) Calculate the degree and significance of the indirect effect using Monte Carlo simulations of the estimated coefficients and their respective standard errors.

#### Missing data

Our protocols include numerous provisions to minimize the amount of missing data, and our team has achieved high retention rates in previous work. However, some data will inevitably be missing. We will use standard methods to evaluate missing data assumptions and to determine alternative analytic strategies if needed. One of three approaches will be used: First, if the proportion of missing data is small and there is evidence that data are missing at random (MAR), all available data will be analyzed using the maximum-likelihood estimation procedures described above. Second, if the proportion of missing data is nontrivial with evidence that data are MAR, multiple imputations for repeated measurements will be used to generate complete data. Third, if there is evidence of a non-MAR mechanism for missing data, pattern mixture models will be used to evaluate and control for the missing data pattern.

#### Power considerations

Given that the proposed analyses for primary outcomes will employ mixed effects modeling of clustered data to assess differences in changes from baseline between treatment groups, power analyses were conducted using Monte Carlo simulations of multi-level models in SAS (SAS Institute Inc., Cary, NC). Expected fixed effect values for effects of interest (e.g., treatment group by time interactions) were obtained from prior research on ESDM treatments and developmental change [109]. We assumed a range of plausible intraclass correlation coefficient (ICC) values for the random effects of child/caregiver dyad (0.3 to 0.5), team (0.1 to 0.25), and region (0.05 to 0.1) based on previous community intervention studies and pilot data and accounted for a 10% dropout rate. We used a type I error level of 5%.

Under each scenario, our proposed sample size of 300 children/caregivers, 100 teams, and 20 centers would provide at least 80% power to detect a standardized improvement in children’s social communication and language of *d* = 0.6. We assumed that 10% of children would not contribute any data; however, the participants who dropped out would have provided some data and will contribute to the analyses. Therefore, our calculations are conservative.

#### Procedures and measures addressing our exploratory implementation aim

We will measure implementation during the three EPIS phases: adoption (recruitment), implementation (ESDM training and delivery), and predicted sustainment (after the research study). We will measure acceptability, appropriateness, and feasibility of the intervention, and provider, family, and organizational characteristics to identify determinants of ESDM implementation. We will use a combination of surveys and structured interviews (see Table 3).

**Table 3 Tab3:** Implementation Measures

Construct	Measure/Indicator
Adoption	Decision to participate in effectiveness study (yes/no)
Implementation	ESDM provider adherence measures [ESDM Fidelity; NDBI Fidelity]; Adaptations to Evidence-Based Practice Scale
Sustainment	Ongoing use of ESDM [PRESS; interviews with managers and providers]
ESDM Appropriateness, Feasibility, Acceptability	Perceived fit of ESDM with agency, provider, and family [AIM; interviews] Caregiver engagement in intervention [session attendance]
Provider Characteristics	Perceived self-efficacy [Autism Self-Efficacy Scale] Provide background experience, previous EBP training
Organization Characteristics	Financing structure and reimbursement; # autistic clients under age 5; Implementation Climate Survey

Acceptability of Intervention Measure (AIM), Intervention Appropriateness Measure (IAM), & Feasibility of Intervention Measure (FIM) [110] determine the extent to which a participant believes an intervention is acceptable, appropriate, and feasible and have strong internal consistency (AIM α = 0.89; IAM α = 0.87; FIM α = 0.89). All participating providers and caregivers will complete these scales every six months during participation. Total score on each scale will be used.

Adaptations to Evidence-Based Practices Scale (AES) [111] is a 6-item scale assessing provider adaptations to EBPs delivered. Providers rate six items using a 5-point Likert scale (0 “not at all,” 4 “a very great extent”) to indicate the extent to which they made each type of adaptation when delivering a specified EBP, including (a) modifying the presentation of EBP strategies, (b) shortening or condensing the pacing of the EBP, (c) lengthening or extending the pacing of the EBP, (d) integrating supplemental content or strategies, (e) removing or skipping components, and (d) adjusting the order of sessions or components.

Provider Report of Sustainment Scale (PRESS) [112] captures provider report of continued use of an intervention. The PRESS has good psychometric properties across multiple interventions and service systems and strong construct validity.

Autism Self-Efficacy Scale for Teachers (ASSET) [113] is a 30-item self-report measure of providers’ beliefs about their ability to implement appropriate teaching strategies when working with autistic children. We adapted the measure for use with community providers who rate their efficacy in carrying out several different assessment, intervention, and evidence-based practices relevant to autism early intervention. Providers rate their self-efficacy using a scale from 0 (*cannot do at all*) to 100 (*highly certain can do*). The total score is calculated as the mean score across the 30 items. Scale internal consistency is 0.96.

The Implementation Climate Scale (ICS) [114, 115] measures employees’ shared perceptions of the policies, practices, procedures, and behaviors that are expected, rewarded, and supported to facilitate effective EBI implementation. The ICS has good psychometric properties across several settings including good internal consistency and good construct validity.

Implementation Interview: Semi-structured interviews will be conducted with regional managers, supervisors, technicians, and caregivers to gather additional information on ESDM feasibility, usability, acceptability, fit (including cultural fit with family needs) and plans for sustainment. We will conduct interviews with a subset of participants until we reach saturation (approximately 30 in each group). Facilitators will follow a semi-structured interview guide [116, 117].

#### Data analysis (exploratory)

Descriptive data regarding feasibility, acceptability and fit and qualitative interview data will be examined every 6 months. These data will be used iteratively through the implementation phase of the trial to make culturally relevant adaptations to the intervention. Adaptations will be carefully logged and tracked and resulting outcomes monitored using recommended methods. We will explore descriptive statistics for the various measures of organizational and provider characteristics and participation and will use predictive models (with multi-level modeling as above) to understand appropriateness, feasibility, and acceptability in the ESDM treatment group. Given that measures of implementation (e.g., provider fidelity) are important for understanding the feasibility of scaling ESDM to CBAs, we will analyze such implementation measures as dependent variables and examine other variables in Table 3 (e.g., organization characteristics, perceived fit) as predictors of individual provider variability in fidelity.

Qualitative Data analysis. NVivo QSR 11 [118] will be used for qualitative analyses. A framework-driven analytic approach will guide the coding process [44, 119]. Coders will use an iterative coding and review process informed by grounded theory [120].

